#### Reporting

For the secondary outcomes, the differences between the treatment arms will be reported as an effect measure (e.g. odds ratio or mean difference) together with a complementary confidence interval and a two-sided statistical test of the effect parameter. A Bonferroni corrected significance level will be used.

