## Estimated sample size and power

Patients will be randomized in a 1:1 fashion. It is anticipated that the rate of the primary endpoint pCR will be approximately 30% in the control arm. We aim to increase the rate of pCR in the experimental arm to 40%, i.e. a 10 percentage points increase, which is regarded clinically relevant since it would translate into improved disease-related outcomes. With a power of 80% and an alpha of 5%, a total of 712 patients have to be included; 356 in each arm. Accounting for a drop-out of 10%, we aim to include 790 patients. Stratification at the moment of computerized randomization will be done based on site of treatment (hospital) and biological tumour subtype (ER+HER2-, ER+HER2+, ER-HER2+, ER-HER2-).

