#### Primary endpoint (pCR)

The primary outcome in this trial (pCR) is dichotomous, and will be assessed through histopathological examination of the surgical specimen after completed NACT. Hence, a multivariable logistic regression model, adjusting for biological tumour type (stratification factor in the randomization) will be used. The treatment effect will be assessed in terms of the resulting odds ratio between the two treatment arms together with a 95% confidence interval and a complementary Wald test. A two-sided statistical test with 5% significance level will be used. Furthermore, differences in pCR rates between the two treatment arms will be explored for each biological tumour type subgroup (ER+HER2-, ER+HER2+, ER-HER2+, ER-HER2-), using an interaction between treatment and biological tumour type.

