All health-related quality of life outcomes are measured as scores that range from 0 to 100, hence the outcomes are continuous. Both the global QoL score as well as the 17 subscales (8 scales reflecting symptoms and 9 reflecting function) will be assessed at four time points: baseline, pre-surgery, 1 and 2 years after surgery. To evaluate QoL scores at each time point both within and between the treatment groups, a mixed model for repeated measures (MMRM) will be used. Treatment, visit, treatment visit interaction and stratification factor biological tumour type will be included in the model as fixed effects, and patient as a random effect. An unstructured covariance matrix will be used to model the within-subject error. If the fit of the chosen structure fails to converge, the following covariance structures will be evaluated, in order, until convergence is reached: toeplitz with heterogeneity, autoregressive with heterogeneity, toeplitz, autoregressive and compound symmetry. Furthermore, differences in change from baseline between the treatment arms will be assessed at each time point by constructing relevant contrasts of the estimated regression coefficients.

1. *Self-reported physical activity*

Physical activity is reported using the Godin-Shephard Leisure-Time Physical Activity Questionnaire (GSLTPAQ) as total minutes per week of training in three intensity levels (light, moderate and intensive) and for weight training. Hence, the outcome is continuous. A mixed model for repeated measures (MMRM) will be used to assess physical activity at four different time points: baseline, pre-surgery, 1 and 2 years after surgery). The model will include treatment, visit, treatment-visit interaction and the stratification factor biological tumour type as fixed effects, and patient as a random effect. An unstructured covariance matrix will be used to model the within-subject error. If the fit of the chosen structure fails to converge, the following covariance structures will be evaluated, in order, until convergence is reached: toeplitz with heterogeneity, autoregressive with heterogeneity, toeplitz, autoregressive and compound symmetry. Physical exercise will be assessed both within and between the treatment groups. Furthermore, differences in change from baseline between the treatment arms will be evaluated at each time point by constructing relevant contrasts of the estimated regression coefficients.

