5. Sick leave is a patient-reported singular measurement at pre-surgery and at 1- and 2-year follow-up (% sick leave). Mean sick leave proportions will be compared between the treatment arms at each time point using a mixed model for repeated measures (MMRM). Treatment, visit, treatment visit interaction and the stratification factor biological tumour type will be included in the model as fixed effects, and patient as a random effect. An unstructured covariance matrix will be used to model the within-subject error. If the fit of the chosen structure fails to converge, the following covariance structures will be evaluated, in order, until convergence is reached: toeplitz with heterogeneity, autoregressive with heterogeneity, toeplitz, autoregressive and compound symmetry. Additionally, since the outcome is most likely not normally distributed, a non-parametric Kruskal-Walllis test will be performed at each time as a sensitivity analysis.
6. *Device-measured physical activity level*

Several continuous outcome measures from the Fitbit activity tracker will be assessed: 1) METs (metabolic equivalents) in low, medium and high intensity activities, respectively, 2) step counts per day and 3) daily active minutes. The main interest is to see if there is a difference between the treatment arms regarding change of physical activity from baseline to pre-surgery (i.e. after intervention and chemotherapy), but also at 1-year follow-up. A mixed model for repeated measures (MMRM) with treatment, visit and the stratification factor biological subtype as fixed effects, and patient as a random effect. An unstructured covariance matrix will be used to model the within-subject error. If the fit of the chosen structure fails to converge, the following covariance structures will be tried, in order, until convergence is reached: toeplitz with heterogeneity, autoregressive with heterogeneity, toeplitz, autoregressive and compound symmetry. Additionally, heart rates at equivalent exertion levels (assessed on the Borg scale) during physical activity will be explored.

1. *Muscle strength*

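### The secondary outcomes are committed to plain Bonferroni, which is valid, but Holm's step-down procedure gives the same familywise error control and never rejects fewer hypotheses

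*Protocol*

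**What the plan says.** The Reporting section of the protocol's statistical analysis plan covers all secondary outcomes at once. Each is to be given as an effect measure "together with a complementary confidence interval and a two-sided statistical test of the effect parameter", and then: "A Bonferroni corrected significance level will be used". The section does not state the overall level to be divided, the number of tests or which tests form the family. For the primary endpoint the level is explicit: "A two-sided statistical test with 5% significance level will be used".

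The section on outcomes, variables and measures numbers nine secondary endpoints. The Secondary endpoints part of the analysis plan expands several of them. For quality of life, the global score and "the 17 subscales (8 scales reflecting symptoms and 9 reflecting function) will be assessed at four time points". For device-measured activity, "Several continuous outcome measures from the Fitbit activity tracker will be assessed". A main score or time point is named for cognition, device-measured activity, muscle strength and cardiorespiratory fitness, but none of these is tied to the correction.

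**The concern.** When a protocol names a multiplicity method, that method should not give power away for nothing in error control. Bonferroni compares every p-value with α/m. Holm compares the smallest with α/m, the next with α/(m−1), and so on up to α, stopping at the first failure. Both hold the familywise error at α under any dependence between the tests. Since no Holm threshold is below α/m, anything Bonferroni rejects Holm also rejects.

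What is at stake is limited. Hypothesis 2 of the protocol says that exercise improves the secondary outcomes, and some true effects that Holm would declare will be missed under Bonferroni. The primary analysis is untouched, and no false-positive rate is inflated.

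**Working it through.** **Inputs from the protocol (Estimated sample size and power).** Control pCR: "the rate of the primary endpoint pCR will be approximately 30% in the control arm". Target: "We aim to increase the rate of pCR in the experimental arm to 40%, i.e. a 10 percentage points increase". Size: "With a power of 80% and an alpha of 5%, a total of 712 patients have to be included; 356 in each arm".

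**Step 1. Reproduce the stated sample size.** With the pooled-variance formula, no continuity correction and mean rate 0.35:

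n per arm = [1.960·√(2·0.35·0.65) + 0.842·√(0.30·0.70 + 0.40·0.60)]² / 0.10² = 355.9, so 356 per arm and 712 in total. This agrees with the protocol.

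**Step 2. Power under Bonferroni.** The protocol gives no effect sizes for the secondary outcomes. As a reference, take an effect with exactly 80% power at two-sided 5%, so its mean z is 1.960 + 0.842 = 2.80. With 356 per arm this is 2.80·√(2/356) = 0.21 SD. Power at level 0.05/m is Φ(2.80 − z for 1 − 0.025/m). The overall 5% is assumed, carried over from the primary endpoint.

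| Tests m | Level 0.05/m | Critical z | Power of reference effect |
|---|---|---|---|
| 1 | 0.05 | 1.960 | 80% |
| 9 | 0.00556 | 2.773 | 51% |
| 98 | 0.00051 | 3.475 | 25% |

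Nine is the number of listed endpoints. Ninety-eight is one literal count of between-arm contrasts: RCB 1, tumour response 2, survival 3, quality of life 18 × 3 = 54, activity minutes 4 × 3 = 12, active/inactive 3, chemotherapy completion 2, admissions 1, cognition total 1, cardiac 1, sick leave 3, tracker 5 × 2 = 10, strength 4, fitness 1.

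**Step 3. Holm against Bonferroni with nine tests.** In these simulations a moderate effect has mean z 2.80 and a strong one mean z 4.5 (4.5·√(2/356) = 0.34 SD). The remaining tests are true nulls. Power is the average over the moderate effects.

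| Real effects among nine | Bonferroni | Holm |
|---|---|---|
| 2 moderate | 51% | 52% |
| 5 moderate | 51% | 55% |
| 3 strong, 3 moderate | 51% | 59% |
| 5 strong, 2 moderate | 51% | 64% |

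The results barely change at correlations of 0.3 or 0.5 between tests. Holm's familywise error stayed below 5% in each case. The gain is easy to explain. Once five strong effects are rejected, the next p-value faces 0.05/4 = 0.0125 instead of 0.00556, and the reference effect has 62% power at that level.

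**Step 4. The same comparison with 98 tests (independent tests, 356 per arm).**

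| Real effects among 98 | Size | Bonferroni | Holm |
|---|---|---|---|
| 10 | 0.2 SD | 21.2% | 21.3% |
| 10 | 0.3 SD | 70.2% | 70.8% |
| 49 | 0.2 SD | 21.0% | 21.9% |
| 49 | 0.3 SD | 70.1% | 74.2% |
| 98 | 0.3 SD | 70.1% | 86.1% |

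Holm's first threshold is still 0.05/98, so the gain is about 0-4 points unless nearly every effect is real.

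**The case against.** The best defence is that Bonferroni is valid and conservative, and that it yields simultaneous confidence intervals directly. The Reporting section pairs every test with an interval, and Holm has no equally simple matching intervals. That stands as a real but small cost. It is weakened because the section never says that its intervals will be adjusted to the corrected level.

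It is also fair to say that Holm matters less than the size of the family. The reference effect goes from 25% power at 98 tests to 51% at nine under plain Bonferroni, and Holm plays no part in that. Cutting down to one contrast per endpoint is a separate choice with its own price, since the other scales lose confirmatory status.

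A reader might infer three stronger things, and the document supports none of them.

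- That the protocol fixes a correction over 98 tests. The number appears nowhere, nine is at least as natural a reading, and the count depends on debatable inclusions. It keeps only the total cognition score, yet includes an analysis labelled as additional. The family is also the kind of detail that a separate statistical analysis plan may hold, so its absence here is not a fault.
- That most real secondary effects would be undetectable. No secondary effect sizes are given, and even at 98 tests with 356 per arm power is 70% at 0.3 SD, 88% at 0.35 SD and 97% at 0.4 SD.
- That switching is free. The interval point above is a cost, though a small one.

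**Conclusion.** The point holds as a minor efficiency improvement. Plain Bonferroni is not wrong, but for tests and error control Holm dominates it under the same absence of assumptions. For a reference effect in a family of nine, the gain runs from about 1 point (51% to 52%) to about 13 points (51% to 64%), depending on how many other effects are real and how strong they are. In a family of about 98 it is about 0-4 points unless nearly all effects are real.

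These figures rest on an overall two-sided 5% level for the secondary outcomes, normally distributed test statistics, 356 analysed per arm where SD units are used, and effect scenarios that are assumed because the protocol gives none. The dominance itself needs none of these assumptions.

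**What to change.** Replace the Bonferroni sentence in the Reporting section with wording such as: *Familywise error across the secondary outcomes is controlled at two-sided 5% with Holm's procedure, applied to the prespecified family; ordinary 95% confidence intervals are shown.* The sponsor sets the family before any between-arm data are seen, here or in the statistical analysis plan. One option is a single named between-arm contrast for each of the nine listed endpoints, with everything else reported as an estimate and interval without a significance claim. That option is a trade-off for the sponsor to weigh, and Holm can be adopted without it.

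The cost is a change of wording, with no new data or patients. The one statistical price is that the 95% intervals will not always agree with the Holm decisions: an unadjusted interval may exclude no effect where Holm does not reject. A short note to that effect in the reports is enough.

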#### Handling missing values and deaths

Experience from previous studies have shown that this group of patients are in general highly motivated to fully participate in trials, including answering questionnaires, undergo physical exams and other assessments. Hence, it is anticipated that the dropout rate and the number of missing values will be low in both treatment arms and that this will be a minor problem in this study. Furthermore, the number of deaths during this relatively short follow-up period is also expected to be low. Nevertheless, sensitivity analysis will be performed where missing values will be assumed to be missing at random, MAR. This assumption will be already accommodated in the mixed models where repeated measurement outcomes will be analysed. For the remaining outcomes multiple imputations, assuming MAR will be performed.

A data monitoring committee consisting of three independent experts will perform a safety analysis with the purpose to assess the recruitment to the trial and the rate of adverse events, and to make sure that patients in the intervention group do not appear to fare significantly worse than patients in the standard of care group. The committee may recommend terminating the study if a significant benefit in favour of one group is shown, such that the HR for intervention versus standard of care significantly (p=0.001) exceeds 1, if the recruitment is so low that that the necessary number of events is unlikely to be reached or if there are serious concerns about unexpected AEs in the intervention group. If the committee determines that it is safe to proceed with the study, the results of the analysis will remain unknown to everyone except the committee members.

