## Statistical analysis plan

All outcomes will primarily be analysed using an intention-to-treat approach, i.e. all study subjects will belong to the treatment group (exercise intervention or control) they were assigned to, disregarding compliance. As sensitivity analysis, all outcomes will also be analysed using a per-protocol approach, meaning that participants in the intervention group who comply with less than 65% of the prescribed physical exercise program or complete less than 40% of the planned neo-adjuvant systemic therapy (around two 3-weekly courses) will be excluded from analysis.

*Covariate adjustment in statistical models*

Guidelines from the European Medicines Agency (EMA) regarding statistics and covariate adjustments recommend that factors that are used to stratify the randomization, i.e. site of treatment and biological tumour type in this trial, should be accounted for in the statistical analysis^35,36^. However, it is also recognized that “limited numbers of subjects per centre will make it impracticable to include the centre effects in the statistical model”. In this trial it is very likely that some of the centres will contribute few patients, which may cause problems in some of the statistical models, in particular for the categorical outcomes (such as the primary endpoint, pCR) where the variability in the outcome may be too small within each site. Hence, the statistical models, described below, will primarily be adjusted for biological tumour type and not for study site. If appropriate and if the data allows (i.e. no convergence problems and not too small subgroups), the site effect will also be incorporated in the models as a random effect in the mixed models and as a fixed factor in the remaining logistic regression models.

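### For the seven outcomes analysed by MMRM, the announced missing-data sensitivity analysis makes the same missing-at-random assumption as the main model and so cannot test it

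*Protocol*

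**What the plan says.** The section on handling missing values and deaths expects little drop-out and few missing values in either arm. It then states that "sensitivity analysis will be performed where missing values will be assumed to be missing at random, MAR". The next sentence reads: "This assumption will be already accommodated in the mixed models where repeated measurement outcomes will be analysed". All other outcomes are given multiple imputation, also under missing at random (MAR).

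The Secondary endpoints section names an MMRM as the main analysis of seven outcomes: health-related quality of life, self-reported physical activity, cognition, sick leave, device-measured activity, muscle strength and cardiorespiratory fitness.

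The general rule at the start of the statistical analysis plan section is that "all study subjects will belong to the treatment group (exercise intervention or control) they were assigned to, disregarding compliance".

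Three other places bear on who will have missing values:
- The adverse-event section classes an event as serious for reporting only if it is related to the intervention.
- The ethics section has participants with a serious adverse event leave the trial.
- The withdrawal section keeps data recorded before withdrawal, unless the participant objects.

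**The concern.** A sensitivity analysis is useful when it changes an assumption that the main result depends on. A likelihood-based mixed model is valid under MAR, so a check defined as assuming MAR, and described as already contained in that model, is the main analysis under another name. It cannot give a different answer.

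The MAR assumption carries weight here. Strength and fitness are measured only at baseline and before surgery. Someone who leaves in between contributes a baseline value alone, and the model predicts the rest from arm, tumour type and that value. It does not see the injury or intolerance that caused the exit. As the protocol is worded, exits after an intervention-related serious adverse event would fall mainly on the exercise arm. If such leavers did worse than their observed data predict, the reported difference would favour exercise, and nothing in the stated plan would show it.

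**Working it through.** **1. What each planned analysis varies for the seven outcomes**

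| Analysis | Changes the missing-data assumption? |
|---|---|
| MMRM (main) | Assumes MAR |
| Missing-data sensitivity analysis | No: MAR, through the same model |
| Multiple imputation | Not applied to these outcomes; also MAR |
| Per-protocol analysis | No: it removes exercise-arm participants with low adherence, or those with too little chemotherapy |
| Kruskal-Wallis test for sick leave | No: it addresses non-normality |

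No row departs from MAR.

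**2. The protocol's own figures**

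The only computed figure is the sample size for pCR: "With a power of 80% and an alpha of 5%, a total of 712 patients have to be included; 356 in each arm". With 30% against 40%, a two-sided 5% level, 80% power and pooled variance under the null:

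n per arm = [1.960 × √(2 × 0.35 × 0.65) + 0.842 × √(0.30 × 0.70 + 0.40 × 0.60)]² / 0.10² ≈ 356, or 712 in total.

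This reproduces. Allowing for 10% drop-out, 712 / 0.90 = 791.1, or 792 with equal arms, against the stated 790; the difference is immaterial. The 10% is a trial-wide allowance made for pCR. No missingness rate, effect size or SD is given for the seven outcomes, so what follows is illustrative.

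**3. Size of a possible bias**

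Let m be the fraction of the exercise arm with no later value and δ the effect in those observed. Assume that unobserved exercise-arm leavers have no benefit and that control-arm leavers behave as MAR predicts.

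- As-assigned effect = (1 − m) × δ
- MAR estimate with a treatment-by-visit term = δ
- Ratio of estimate to as-assigned effect = 1 / (1 − m)

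| m | 1 / (1 − m) | Overstatement |
|---|---|---|
| 5% | 1.053 | 5% |
| 10% | 1.111 | 11% |
| 20% | 1.250 | 25% |

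For example, δ = 0.25 SD with m = 10% gives an as-assigned effect of 0.90 × 0.25 = 0.225 SD, a gap of 0.025 SD.

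**4. Simulation check**

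Two visits, unstructured covariance, N = 790, 400 runs, δ = 0.30 SD, correlation 0.6. Both arms drop out at random at the rate shown, and exercise-arm leavers have no benefit.

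| Drop-out | As-assigned effect | MMRM with treatment-by-visit term | Treatment coefficient without that term |
|---|---|---|---|
| 10% | 0.270 | 0.302 | 0.137 |
| 20% | 0.240 | 0.297 | 0.128 |

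With the interaction, the model returns the effect in those observed, as the formula predicts. Without it, the treatment coefficient blends the baseline and follow-up differences and falls below the as-assigned effect.

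The protocol writes the interaction for quality of life, self-reported activity and sick leave. It does not list it for cognition, tracker activity, strength or fitness, although change from baseline is the stated interest there. The overstatement applies to those four only if the change contrast is in fact estimated with that term.

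**The case against.** The strongest reply is that the section hides nothing. It says openly that the mixed models already assume MAR, so the additional work is meant for the remaining outcomes. A departure from MAR could be left to a separate analysis plan, which is not at hand. This is fair as to intent, and the absence of a further method would not be a finding by itself. What stands is that the protocol states what its missing-data sensitivity analysis is, and for seven outcomes the stated analysis cannot do that job.

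Stronger readings are tempting and are not supported:

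- **A contradiction with intention to treat.** A reader might infer that MAR breaks the rule on disregarding compliance. That rule fixes the group in which a participant is analysed, and an MMRM by assigned arm obeys it. There is at most a tension with the aim of intention to treat for people who leave unobserved.
- **Non-adherers credited with benefit.** The Population section has every participant tested before and after chemotherapy. A non-adherer who is still assessed enters with her own data.
- **A general bias towards exercise.** The percentages assume that leavers have no benefit at all, that control-arm missingness is harmless and that the interaction is fitted. If control-arm leavers also did worse than predicted, the net bias would be the difference between the arms and could shrink or reverse. With the four models as written, the treatment coefficient errs the other way.

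Imputing every missing exercise-arm value from controls would also be too broad: someone who completed the programme and missed a two-year questionnaire should not be treated as a leaver.

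**Conclusion.** The point holds in limited form. For the seven MMRM outcomes the stated missing-data sensitivity analysis duplicates the main analysis and cannot test MAR. The per-protocol and Kruskal-Wallis analyses do not fill the gap.

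The possible distortion is modest at the low missingness the protocol expects: about 5% of the effect at m = 5% and 11% at m = 10%, under the assumptions in the working. These are illustrations, not predictions, because the protocol gives neither a missingness rate nor an effect size for these outcomes. Only secondary outcomes are concerned. This is a cheap improvement worth making, not a threat to the trial's main conclusion.

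**What to change.** Keep the MMRM as the main analysis. For these seven outcomes, replace the MAR sensitivity sentence with a named departure from MAR, for example:

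*For outcomes analysed by MMRM, missing later values of exercise-arm participants who stopped the intervention or left the trial, and have no later assessments, will be multiply imputed with reference to the control arm. For the pre-surgery strength and fitness contrasts, a delta-adjusted tipping-point analysis will be applied to missing values in both arms.*

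The date and reason for stopping or leaving must be recorded well enough to identify the first group. The strength and fitness models should also state the treatment-by-visit term, so that the contrast under test is the change from baseline.

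The cost is a little programming and no new outcome assessments. The reference-based estimate will be somewhat smaller and conservative, which is acceptable in a sensitivity analysis. The pCR analysis does not change. The amendment is best made before results by arm are seen.
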